### Objectives {7}

The primary objective of this trial is to evaluate the effectiveness and safety of the Care Anywhere with Community Paramedics (CACP) program with respect to increasing days alive spent outside the ED or hospital between the day after randomization and 30 days thereafter among patients (1) being treated in the ED or hospital but clinically stable for ambulatory care with CP support and (2) being treated in the pre-hospital setting (e.g., outpatient clinic or home) but requiring a higher level of care that would usually prompt a referral to the ED/hospital but could be managed by the CACP program. Secondarily, we will examine the CACP program with respect to reach, adoption, acceptability, implementation, and sustainability from the patient, CP, referring clinician, and health system administrator perspectives; patient satisfaction with the program; patient experience with treatment and self-management, i.e., treatment burden; patient safety outcomes at 30 days (falls, medication errors, ED visits, hospitalizations, death); and long-term acute care utilization (i.e., ED visits, hospitalizations) outcomes at 6 and 12 months. This hybrid approach to exploring implementability preparatory to and during an effectiveness trial is aimed at identifying implementation issues so strategies to address them can be incorporated into trial adaptations or future implementation [16, 17].

There are three study aims:Aim 1: Identify potential facilitators and barriers to implementation and refine workflows in pre-implementation phaseAim 2: Evaluate CACP effectiveness and safety, compared to usual care, as well as implementation outcomesAim 3: Assess patient, CP, clinician, and administrator acceptability, satisfaction, and perceived sustainability

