### Outcomes {12}

Trial outcomes for the three specific aims are detailed in Tables 1 and 2. Aim 1 is a formative evaluation of the implementation context that seeks to rapidly identify and address anticipated barriers and challenges, as well as identify opportunities that could impact the successful implementation of the pragmatic trial and the CACP program. It involves qualitative interviews with CPs, clinicians and other members of the health care team, and administrators, in the 3-month period directly before trial enrollment commences with anticipated qualitative outcomes related to acceptability and feasibility, as well as detailed recommendations for targeted actions.

**Table 1 Tab1:** Elements of primary and secondary outcomes

Domain	Specific measurement	Specific metric	Method of aggregation	Time point
Potential barriers to CACP implementation (aim 1)	Qualitative interviews	Perspectives on acceptability, feasibility, and workflow impact	Content analysis by construct by role, e.g., CP, clinician, administrator	Prior to the start of the enrollment period (− *T*_1_)
CACP effectiveness (aim 2 primary)	EHR review	Days alive out of ED or hospital 0 and *T*_3_	The number of days the patient was alive and out of the ED or hospital (not in hospital, excluding planned hospital admissions for scheduled surgeries, procedures, and/or treatments) between 0 and *T*_3_	Comparison between the groups will be made at *T*_3_
CACP effectiveness (aim 2 secondary)	EHR review	Unplanned ED visits, hospitalizations, or death (composite endpoint and individual)	The number of events per participant per 30 days, the percent of participants with events within 30 days, and time to event(s). Will report as a composite outcome and individually	Comparison between the groups at *T*_4_ and *T*_5_
CACP effectiveness (aim 2 exploratory)	EHR review	SNF care	The percent of participants admitted to SNF within 30 days of randomization and duration of SNF stay	Comparison between the groups will be made at *T*_3_
CACP safety (aim 2 secondary)	EHR review	Unplanned hospitalizations, ED visits, falls with injury, medication errors with harm, and death	The percentage of patients with events within 30 days, the total number of events within 30 days, and time to event(s). Will report as a composite outcome and each outcome individually	Comparison between the groups at *T*_3_ and the day after randomization to *T*_3_

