#### Sample size {14}

For aim 1, the sample size will be assessed iteratively during data collection and analysis with the aim of ensuring that the implementation plan is feasible and meets the needs of key user groups. We anticipate up to 25 interviews in the pre-implementation phase for aim 1.

The aim 2 sample size was calculated on the basis of the primary hypothesis. Pilot studies of CP care on days out of ED or hospital in the first 30 days yielded an estimated mean of 27 days in the intervention group. A difference of 2 days was considered clinically important by stakeholders. We have powered this trial to detect a 10% improvement in the primary outcome. To detect a mean difference of 2 days out of ED or hospital at 30 days with a two-sided significance level of 0.05 and a power of 80% with equal allocation to two arms would require 120 patients per group assuming a pooled standard deviation of 5 days. The standard deviation was estimated by assuming the range of measurement will span approximately six standard deviations. Because the primary endpoint is assessed at 30 days and based on the coverage of the EHR, we expect minimal drop-out and missing data. Multiple imputation will be used if more than 20% of patients have missing data on the primary outcome. Aim 3 qualitative inquiry will use a purposeful sampling approach to intentionally select participants who can provide information about their experiences with the program. Based on the past experience of this team, the heterogeneity of expected patient situations, and the scope of this inquiry, we anticipate conducting approximately 25 patient interviews. We anticipate up to 35 clinicians and other stakeholders will also complete aim 3 interviews.

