## Statistical methods

### Statistical methods for primary and secondary outcomes {20a}

#### Aim 1

We will use methods of rapid qualitative analysis, guided by constructs in the Consolidated Framework for Implementation Research (CFIR) [22]. Members of the study team will meet to review notes and audio recordings from interviews and discuss issues that may impact implementation, including those that should be addressed before trial enrollment commences. Notes will be summarized in a template guided by the CFIR framework and imported into qualitative software (NVivo, QSR International) for data management. Summaries will be presented at biweekly study team meetings for discussion of potential actions, including changes to the implementation plan.

#### Aim 2

The main analysis of the primary outcome will be based on the intention-to-treat (ITT) principle, with all patients randomized to CACP compared to all patients randomized to usual care. The ITT sample will comprise all patients who were randomized and completed the baseline assessment. The primary outcome (CACP effectiveness) is defined as the number of days the patient was alive and outside of the ED or hospital (excluding planned hospital admissions for scheduled surgeries, procedures, and/or treatments). Outcomes will also be analyzed in the per-protocol subset. The per-protocol sample will comprise all patients in the ITT arm except for those who did not follow protocol, i.e., patients who did not receive CP services in the intervention arm.

The mean number of days out of the ED or hospital for the intervention group will be compared to that of the control arm. Statistical significance, and a two-sided confidence interval for the difference between arms, will be assessed by using the two-sample *t* test. The distributional assumptions for the test will be assessed by calculating the skew and kurtosis for the bootstrap distribution of the sample difference between means. The Hodges-Lehman shift estimator for the Wilcoxon rank-sum test will be used if the absolute value of the skew or kurtosis-minus-three are greater than 1.5.

Other continuous outcome measures will be assessed by the same method as the primary outcome measure. Categorical measures will be assessed by using the Pearson chi-square test, or the Fisher exact test will be used if the minimum expected cell count is less than five.

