Throughout the course of the study, we will also monitor AEs in both study arms and may suspend accrual if patients are experiencing a large number of adverse events. In particular, we will temporarily suspend accrual if, at any time, observed events meet the following criteria: (1) If, within the first 30 patients, 2 or more patients in the CACP arm than the usual arm experience a SAE, the study will be paused for review by the DSMB; (2) if, after the first 30 patients, the proportion of participants in the CACP arm who experience an SAE is ≥ 10% greater than the proportion of participants experiencing SAE in the usual care arm, the study will be paused for review by the DSMB.

If unexpected adverse event profiles are observed which do not meet the above criteria, but are worrisome, we may still consider temporarily suspending accrual. Adverse event-stopping rules may be modified if, during the study, new information becomes available, which suggests that such a modification is necessary, or, if after temporarily stopping accrual, the above rule is found to be overly conservative.

Reports containing efficacy, AE, and administrative information will be compiled and presented to the DSMB every three months.

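### Safety event percentages are compared by a test of no difference alone, which at 120 per arm puts no bound on excess harm

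*Protocol article*

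**What the plan says.** The Objectives section {7} begins: "The primary objective of this trial is to evaluate the effectiveness and safety of the Care Anywhere with Community Paramedics (CACP) program", tied to days alive outside the ED or hospital. It then places "patient safety outcomes at 30 days (falls, medication errors, ED visits, hospitalizations, death" among the secondary aims. Table 1 under Outcomes {12} agrees with that lower rank. The row is labelled "CACP safety (aim 2 secondary", its components are "Unplanned hospitalizations, ED visits, falls with injury, medication errors with harm, and death", and they are summarised as "The percentage of patients with events within 30 days, the total number of events within 30 days, and time to event(s", each alone and as a composite, with a comparison between arms.

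The Aim 2 part of the Statistical methods section {20a} gives the primary outcome a two-sample t test with a two-sided confidence interval and extends that method to other continuous measures. For proportions it says "Categorical measures will be assessed by using the Pearson chi-square test, or the Fisher exact test will be used if the minimum expected cell count" falls below five. No interval is attached. The same section mentions logistic regression for covariates and descriptive statistics.

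On size, the Sample size section {14} says "The aim 2 sample size was calculated on the basis of the primary hypothesis" and arrives at 120 per group. The only numerical safety threshold is in the Adverse event section {22}: after the first 30 patients, accrual is paused for DSMB review if "the proportion of participants in the CACP arm who experience an SAE is ≥ 10% greater than the proportion of participants experiencing SAE" under usual care.

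**The concern.** A test of no difference can signal harm when it rejects. When it does not reject, it says nothing about how much harm remains possible, and that depends on the event rate and the sample size. Here the sample size was chosen for mean days, not for event proportions. The section therefore gives an interval where the trial is reasonably precise (days, survey scores) and omits it where the trial is imprecise (falls with injury, medication errors with harm, death).

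The programme moves care from the ED or hospital into the home, and the Dissemination and Discussion sections foresee expansion if results are favourable. A reader of the results will want to know how large an excess of harm the data rule out. The stated test does not answer that.

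**Working it through.** **1. The plan's own figure.** Inputs from Sample size {14}: difference 2 days, SD 5 days, two-sided alpha 0.05, power 80%. The normal formula gives n = 2 × (1.96 + 0.84)² × 5² / 2² ≈ 98.1, so 99 per group (100 with the t distribution). The stated 120 gives 87% power and is not reproduced from these inputs. That is a separate matter. I take 120 per arm as given, and no safety event rate enters the calculation.

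**2. Method for the safety test.** I enumerated all 121 × 121 pairs of event counts at 120 per arm. The rule in {20a} was applied to each pair (uncorrected Pearson chi-square, or Fisher if the minimum expected count is below five, two-sided 0.05). A detection was counted only when the result was significant in the direction of harm. Usual-care rates are assumptions.

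**3. Chance of missing a true 10-point excess.**

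| Usual care | CACP | Missed |
|---|---|---|
| 2% | 12% | 10% |
| 5% | 15% | 24% |
| 10% | 20% | 41% |
| 20% | 30% | 57% |
| 30% | 40% | 63% |
| 50% | 60% | about two thirds |

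Hand check at 20% v 30% by normal approximation: null SE = √(2 × 0.25 × 0.75 / 120) = 0.0559; alternative SE = √((0.20 × 0.80 + 0.30 × 0.70) / 120) = 0.0555. Power = Φ((0.10 − 1.96 × 0.0559) / 0.0555) = Φ(−0.17) ≈ 43%, so 57% missed.

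**4. Chance of missing a true relative increase.**

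| Usual care | CACP | Missed |
|---|---|---|
| 2% | 4% | 93% |
| 3% | 6% | 83% |
| 5% | 10% | 68% |
| 10% | 20% | 41% |
| 2% | 6% | 72% |

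**5. What an interval would show.** Differences are CACP minus usual care, with Newcombe 95% limits built from the Wilson limits of each arm.

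- 12/120 v 6/120: pooled rate 0.075, SE = √(2 × 0.075 × 0.925 / 120) = 0.034, z = 0.05 / 0.034 = 1.47, p = 0.14. The Wilson limits are 5.8% to 16.7% and 2.3% to 10.5%. Upper limit = 0.05 + √((0.167 − 0.100)² + (0.050 − 0.023)²) ≈ 0.122; lower limit = 0.05 − √((0.100 − 0.058)² + (0.105 − 0.050)²) ≈ −0.019. The interval is −1.9 to +12.2 points.
- 48/120 v 36/120: p = 0.10, interval −2.1 to +21.7 points.
- 36/120 in both arms: upper limit still +11.5 points.

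All three comparisons are non-significant, yet each leaves an excess of more than 11 points possible.

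**The case against.** The case against has several sound parts.

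- This is a condensed article and an analysis plan may exist. A missing interval for risk differences would not, taken alone, be a finding. But the article does state a method for these proportions, next to a different one for continuous outcomes, and the point concerns that stated choice.
- The safety outcomes are secondary in both Objectives and Table 1, and secondary outcomes need not be powered. That stands. It is a reason to report precision, not to enlarge the trial.
- A reader might infer that chi-square or Fisher is the only safety assessment and would be the only basis for calling the programme safe. The documents do not support this. Event counts, time to event, logistic regression, adjudication and DSMB review are also described, and the protocol nowhere says a non-significant test will be read as safe. Still, none of these comes with a stated bound on excess event risk. The interval for the primary outcome concerns mean days. It covers ED visits, hospitalizations and deaths only indirectly, and falls and medication errors are not among its components.
- A reader might infer that 120 per arm would usually miss a relevant harm. That is too broad. A 10-point excess is found more often than not at usual-care rates of 10% or below, and the protocol gives neither a base rate nor a relevant difference.
- A reader might take the 10% SAE excess as the protocol's own limit of acceptable harm. It is a trigger for pausing and review, it acts on the observed difference without a test, and the protocol allows that it may prove overly conservative. It is not a margin for the final analysis.

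**Conclusion.** The point holds in a limited form. Safety is named in the primary objective, and the method stated for comparing safety event percentages cannot say how much excess harm is excluded. At 120 per arm this matters in two situations: relative increases in rare events (68% to 93% of doublings missed at usual-care rates of 2% to 5%) and absolute increases in common ones (57% to about two thirds of 10-point excesses missed at rates of 20% to 50%). It matters less for a 10-point excess at rates of 10% or below.

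These figures rest on assumed event rates, 120 analysed patients per arm, and a 10-point difference used only as an illustration. The primary analysis is unaffected. The weakness is in what could be said about safety at the end, and it should be corrected in the analysis wording.

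**What to change.** In {20a}, add for each safety component (death, falls with injury, medication errors with harm, unplanned hospitalization, ED visit) and for the composite: the CACP minus usual-care risk difference with a two-sided 95% confidence interval, for example Newcombe. State that the safety statement rests on the interval, in particular its upper limit, and that p > 0.05 will not be reported as evidence of safety. The chi-square or Fisher p-value can stay as an addition. No formal margin is required, and the pause trigger in {22} should not be adopted as one.

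The cost is a few sentences and one interval per outcome, from data already collected and with no extra patients. The downside is a less favourable safety statement, because at this sample size several components will probably have to be reported as inconclusive.

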### Interim analyses {21b}

There will be no interim analysis of effectiveness or implementation outcomes for the purpose of early stopping of the trial. Interim analyses will be limited to those completed for safety monitoring. They will be conducted by the study statistician, and the results will be made available to the Data and Safety Monitoring Board (DSMB). The results will not be blinded to the DSMB as they will be used to ensure safety of continuing the trial. Analyses will be conducted independently of the investigators.

### Methods for additional analyses (e.g., subgroup analyses) {20b}

Heterogeneity of treatment effects analyses will be completed for the subgroup categories of patient age (< 45 years, 45–64 years, ≥ 65 years), patient gender (male, female), patient race/ethnicity (non-Hispanic White, non-White), patient rurality (rural, non-rural), referral source (pre-hospital, ED, hospital), reasons for referral, and types of services delivered (as indicated in the patient referral tracker). The analyses will be performed for the primary outcome measure by using a general linear model with terms for arm, subgroup category, and treatment by subgroup category interaction.

### Methods in analysis to handle protocol non-adherence and any statistical methods to handle missing data {20c}

Primary analyses will be conducted using an intention-to-treat approach. Secondary analysis will be conducted using the per-protocol approach, where patients randomized to the CACP arm who never received the intervention or did not complete the intervention (i.e., did not respond to CP service calls to be scheduled and had to be administratively discharged from the CACP program) will be excluded. Patients randomized to the control condition will not be eligible to receive CP services during the 30-day follow-up period. We will confirm this using an EHR review and exclude any patients who received CP care during that period.

Missing data: For the primary outcome, missing data (e.g., loss to follow-up, withdrawal, death) are expected to be minimal at 30 days, as data are collected from the EHR and are part of the standard of care. Primary analyses will be conducted on the intention-to-treat population. For missingness greater than 20%, multiple imputation will be used.

If patients self-report on *T*_3_ surveys any hospitalizations or ED visits not captured in the EHR, the study staff will confirm those visits using phone follow-up. We will report the percentage of missing data for all primary and secondary outcomes at each time point, as well as for individual survey items. For validated measures with multiple items, we will follow scoring guidance for missing data.

### Plans to give access to the full protocol, participant-level data, and statistical code {31c}

The full protocol, de-identified datasets, and statistical code may be made available from the corresponding author upon reasonable request and appropriate resources after the final publication of results.

### Oversight and monitoring

#### Composition of the coordinating center and trial steering committee {5d}

The trial will have oversight by a steering committee, which includes the principal investigator and co-investigators. The steering committee is responsible for reviewing and approving any modifications to the study protocol. The committee will meet monthly to review the study progress, including trial recruitment. They will also review data on three categories of adverse events (AE) and report serious adverse events (SAE) to the DSMB and IRB.

#### Composition of the data monitoring committee, its role, and reporting structure {21a}

This study will use a DSMB that is independent from the study sponsor and investigator team. Its members represent diverse areas of expertise that are key components of the proposed study, specifically emergency, hospital medicine, and biostatistics. The DSMB will meet via videoconference every three months.

#### Adverse event reporting and harms {22}

The study team will monitor for AE in both groups including ED visits, unplanned hospitalizations, deaths, falls with injury, and medication errors. SAEs for this study are any events that result in death, are life-threatening or place the participant at immediate risk of death from the event as it occurred, result in an ED visit or hospitalization, or cause persistent or significant disability or incapacity. The study statistician will check for hospitalizations, ED visits, and deaths on a weekly basis. Additionally, study coordinators review patient charts over the course of the study volunteer period, ensuring all adverse events are properly reported to the IRB as required per protocol. AEs and SAEs will be tracked in an Excel adverse event tracking log by the study research coordinators. AE and SAE that occur will be reviewed by the adjudication committee, which is comprised of clinical experts in hospital medicine, emergency medicine, cardiology, primary care, and paramedicine. The principal investigator is not a member of the adjudication committee.

The adjudication committee will assess the relationship of all AEs to the study intervention, based on temporal relationship and clinical judgment. The degree of certainty about causality will be graded using the categories below.Definitely related—There is clear evidence to suggest a causal relationship, and other possible contributing factors can be ruled out. The clinical event, including an abnormal laboratory test result, occurs in a plausible time relationship to study intervention administration and cannot be explained by concurrent disease or other drugs or chemicals. The response to the withdrawal of the study intervention (dechallenge) should be clinically plausible. The event must be pharmacologically or phenomenologically definitive, with the use of a satisfactory rechallenge procedure if necessary.Possibly related—There is some evidence to suggest a causal relationship. However, other factors may have contributed to the event (e.g., the participant’s clinical condition, other concomitant events). Although an AE may rate only as “possibly related” soon after discovery, it can be flagged as requiring more information and later be upgraded to “probably related” or “definitely related,” as appropriate.Not related—The AE is completely independent of study intervention, and/or evidence exists that the event is definitely related to another etiology. There must be an alternative, definitive etiology documented.

All AEs related to the intervention will be reviewed in duplicate by two members of the adjudication committee, and their severity will be graded using the following guidelines:Mild–events that require minimal or no treatment and do not interfere with the participant’s daily activities.Moderate—events that result in a low level of inconvenience or concern with therapeutic measures. Moderate events may cause some interference with functioning.Severe—events that interrupt a participant’s usual daily activity and may require systemic drug therapy or other treatment. Severe events are usually potentially life-threatening or incapacitating. Of note, the term “severe” does not necessarily equate with “serious.”

Disagreements in adjudication will be reviewed by a different member of the adjudication committee. Final adjudication results will be compiled by the study coordinator and used for analysis and DSMB reporting purposes.

Throughout the course of the study, we will also monitor AEs in both study arms and may suspend accrual if patients are experiencing a large number of adverse events. In particular, we will temporarily suspend accrual if, at any time, observed events meet the following criteria: (1) If, within the first 30 patients, 2 or more patients in the CACP arm than the usual arm experience a SAE, the study will be paused for review by the DSMB; (2) if, after the first 30 patients, the proportion of participants in the CACP arm who experience an SAE is ≥ 10% greater than the proportion of participants experiencing SAE in the usual care arm, the study will be paused for review by the DSMB.

If unexpected adverse event profiles are observed which do not meet the above criteria, but are worrisome, we may still consider temporarily suspending accrual. Adverse event-stopping rules may be modified if, during the study, new information becomes available, which suggests that such a modification is necessary, or, if after temporarily stopping accrual, the above rule is found to be overly conservative.

Reports containing efficacy, AE, and administrative information will be compiled and presented to the DSMB every three months.

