#### Intervention description {11a}

The CACP program is an extension of an established care delivery model offered by the Mayo Clinic Ambulance Service. In the CACP program, the referring clinician identifies services or interventions clinically required for the patient. This may include patient education, clinical reassessment, laboratory specimen collection, medication administration, wound care, and other services within the CP scope of service. Visits are limited to up to two per day and are generally no more than 2 h in duration. The referring service or the patient’s primary care provider (PCP) or another ambulatory care provider, as appropriate, oversees clinical care with the support of the CP medical director. CPs will communicate with the referring service and/or their medical director as appropriate (usually after every visit but individualized based on the patient’s need and instructions provided by the referring service) via EHR inbox messages, the EHR chat function, or telephone. Patients will graduate from the program once the goals outlined in the referral are completed. Upon graduation, the CP team will communicate directly with a clinician assuming the patient’s care (e.g., PCP).

The CACP program will be available to patients at no cost, and services provided by CPs under this trial will not be submitted to participating patients’ insurance. If CPs facilitate or assist with a service performed by other members of the health care system, the services performed by others will be processed by the patient’s insurance as per usual procedures. For example, if a patient is seen for clinical assessment, venipuncture with laboratory sample collection, and administration of intravenous fluids, the assessment, venipuncture, IV start, and IV fluids themselves will be free to the patient. However, the analysis of the blood sample conducted by a clinical laboratory after it is collected and delivered by CPs will be processed through insurance. In contrast, point-of-care testing performed by CPs will be at no cost to the patient.

Participants randomized to usual care will be treated without consideration of CP care options. We anticipate that most will be referred to the ED and admitted to the hospital or have alternative care pathways (e.g., home health agency, SNF, frequent clinic visits) to meet their clinical needs. The start time for both cohorts will be the day after randomization.

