#### Participant timeline {13}

The schedule of enrollment, intervention, and assessment for patient participants is shown in Table 3. Adults (age ≥ 18 years) being treated in the pre-hospital environment (e.g., outpatient clinic or home), ED, or hospital will be identified by their treating clinicians as needing and being clinically appropriate for outpatient management with supportive services provided by the CP team. Clinicians will query patient interest, and a member of the study team will subsequently approach, consent, and enroll patients. Subsequent to consent, they will be randomized 1:1 to CACP versus continued usual care, with stratification by source of referral (pre-hospital versus ED versus hospital) and location (Minnesota versus Wisconsin, corresponding to the two different CP teams delivering the intervention). Participants randomized to CACP will be eligible to receive CP services as ordered by the referring clinician. Participants randomized to usual care will continue to receive care as they would otherwise, including being referred to the ED (for patients in the pre-hospital setting), admitted to the hospital (for patients in the ED), or remain in the hospital (for patients already in the hospital) as appropriate.

**Table 3 Tab3:** Flow of study procedures for patient participants

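### The SAE definition omits prolongation of an existing hospital stay, so the SAE-based pause rules are asymmetric against CACP among patients referred from hospital

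*Protocol article*

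**What the plan says.** All references are to the Protocol article.

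- **Seriousness criteria** (Adverse event reporting and harms {22}). The definition opens "SAEs for this study are any events that result in death, are life-threatening or place the participant at immediate risk of death". It is completed by events that "result in an ED visit or hospitalization, or cause persistent or significant disability or incapacity". The list is closed, and no other section adds to it.
- **Who is in hospital.** The Objectives include patients "being treated in the ED or hospital but clinically stable for ambulatory care with CP support". Hospital is one of three referral strata (Sequence generation {16a}). Under usual care these patients "remain in the hospital (for patients already in the hospital) as appropriate" (Participant timeline {13}). Recruitment {15} asks clinicians to refer patients whom CACP would allow to leave sooner.
- **What SAEs are used for** (section {22}). Accrual pauses for DSMB review if, within the first 30 patients, the CACP arm has at least two more patients with an SAE than usual care. After that it pauses if "the proportion of participants in the CACP arm who experience an SAE is" at least 10% greater than in usual care.
- **What else is recorded.** Section {22} also states: "The study team will monitor for AE in both groups including ED visits, unplanned hospitalizations, deaths, falls with injury, and medication errors". Table 1 makes falls with injury and medication errors with harm secondary safety outcomes, compared between arms.

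**The concern.** A pause rule that compares arms needs one yardstick for both. Here the yardstick depends partly on where the patient is, and location is what the allocation changes. A patient already admitted cannot have a harm that results in hospitalization in the ordinary sense; a harm that is not fatal, life-threatening or disabling can only lengthen the stay. A patient at home with the same harm may go to the ED, and then it is an SAE.

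At stake is the monitoring comparison. In the hospital stratum CACP could appear to have more SAEs than usual care with no true difference in harm, making a pause more likely.

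**Working it through.** The plan gives no figure for this, so the check is first a reading of the text and then an illustration.

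**1. The same harm in two places (hospital-referred patients)**

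| Harm | Still in hospital (mainly usual care) | At home after discharge (mainly CACP) |
|---|---|---|
| Fatal, life-threatening or disabling | SAE | SAE |
| Not so, but lengthens the stay, or leads to an ED visit or readmission | Not an SAE | SAE |
| Neither of these | Not an SAE | Not an SAE |

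Only the middle row differs. The gap also applies to a CACP patient who is in hospital when harmed, but by design such patients are fewer in that arm of this stratum.

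**2. How much this could move the pause rules (assumptions only)**

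The document gives no SAE rate, no stratum mix and no share of harms serious only through prolongation. Assume:

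- *p*: true proportion of patients with a serious harm under a symmetric definition, equal in both arms;
- *h*: share of patients referred from hospital;
- *f*: share of usual-care patients with serious harm in that stratum who qualify only through prolongation and have no other SAE.

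The usual-care SAE proportion is then *p*(1 − *hf*), and the false gap is *p* × *h* × *f*. For example, 0.20 × 0.50 × 0.50 = 0.05, or 5 percentage points.

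Pause probabilities are exact binomial at a single look. Rule 1 uses 15 v 15 patients and a difference of at least 2. Rule 2 uses 60 v 60 and a difference of at least 0.10, reading the 10% as percentage points.

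| *p* | *h* | *f* | False gap (points) | Rule 1 | Rule 2 |
|---|---|---|---|---|---|
| 0.10 | 0.30 | 0 | 0 | 17% | 5% |
| 0.10 | 0.30 | 0.25 | 0.75 | 19% | 6% |
| 0.10 | 0.30 | 0.50 | 1.5 | 20% | 7% |
| 0.20 | 0.50 | 0 | 0 | 25% | 10% |
| 0.20 | 0.50 | 0.25 | 2.5 | 30% | 17% |
| 0.20 | 0.50 | 0.50 | 5 | 36% | 27% |
| 0.30 | 0.70 | 0 | 0 | 28% | 14% |
| 0.30 | 0.70 | 0.25 | 5.25 | 39% | 32% |
| 0.30 | 0.70 | 0.50 | 10.5 | 51% | 57% |

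The rows with *f* = 0 are the rules under a symmetric definition with equal true harm. The shift runs from negligible to large, depending wholly on inputs that the document does not supply.

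**3. The other two strata**

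For usual care the Intervention description {11a} says "We anticipate that most will be referred to the ED and admitted to the hospital or have alternative care pathways". The SAE definition does not say whether that expected index ED visit or admission is excluded. If it is counted, usual-care SAEs in the pre-hospital and ED strata rise, which is the opposite direction. The table ignores this, so it is not an estimate of the trial-wide bias.

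**The case against.** **The harms are still recorded.** A reader might infer from the omission that harms to usual-care inpatients go uncounted, or that the risks of staying in hospital are left out of the safety comparison. The document does not support that. Injurious falls and medication errors are monitored as adverse events in both arms and compared as safety outcomes, with no condition on location or seriousness. Fatal, life-threatening and disabling harms are SAEs anywhere. A longer stay also lowers the primary outcome. All of this stands, but it does not cure the pause rules, whose numerical triggers use SAEs only.

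**The DSMB sees more than SAEs.** It is unblinded, has hospital-medicine expertise and receives quarterly efficacy and adverse-event reports. A pause leads to DSMB review, not to termination, and the plan lets the rule be modified if found overly conservative. This stands and limits the practical harm.

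**The direction is not known for the whole trial.** A reader might infer that the usual-care SAE proportion is understated across the arm. As step 3 shows, index care in the other strata could push the other way. This stands. An opposite distortion elsewhere would not, however, make the hospital-stratum comparison fair.

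**The size is unanchored.** Enrolled patients must not need hospital-level care beyond what CPs can deliver, so high rates of stay-prolonging harm may be unlikely. The rules also count participants, so a patient with another SAE is already counted. Both stand, and no magnitude should be claimed.

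**Conclusion.** The concern holds in a limited form. The stated SAE criteria omit prolongation of an existing hospitalization. In the hospital-referral stratum this makes SAE status depend on location, and so on allocation, for harms serious on no other ground. The pause rules are asymmetric there, against CACP.

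The asymmetry rests on the text alone; its size does not. The illustrative false gap of 0.75 to 10.5 percentage points assumes the harm rate, the hospital share, the share of prolongation-only harms, and that the CACP patients concerned are at home when harmed. It shows that the effect could be trivial or could approach the 10% trigger; it is not an estimate. The net direction across all three strata is undetermined, and the primary effectiveness analysis is unaffected.

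**What to change.** In Adverse event reporting and harms {22}, extend the hospitalization criterion with the words 'or prolong an existing hospitalization'. Apply it to both arms from randomization, with the existing adjudication committee deciding whether an event prolonged a stay. Use the amended definition in the DSMB tables and in both pause comparisons. If events already logged are re-classified, do so in both arms, with adjudicators blinded to allocation.

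The cost is one clause and some re-reading of charts that coordinators already review. The small downside is that prolongation is a judgement about how long the stay would otherwise have been. It would arise mostly for usual-care inpatients, and Who will be blinded {17a} concedes that adjudicators may see CP notes in the record. Blinding will therefore be imperfect.
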